### Data analysis

The R programming language (R version 4.4.1) will be used to analyse the data (
R Core Team, 2022;
https://www.r-project.org/). Details of dropped-out/withdrawn patients will be recorded. Missing data, drop-outs, non-compliance, and adverse events will be managed in collaboration with the biostatistician and supervisor. The data of all randomized participants will be analysed using intent-to-treat analysis and mixed model multivariate analysis. Information regarding solicited and spontaneously reported adverse events and other unintended effects of trial interventions or trial conduct will be documented and reported to the DMC as well as the ethics committee of the institution. The DMC will have access to interim analysis results and will take the decision to terminate the trial in case of unreasonable morbidities or mortalities among the recruited participants during the trial. Information obtained from the interim analysis may be used for enhancing trial efficiency by updating design and/or sample size adjustments, this will be done as per the suggestions of DMC and after due approval from the funding agency. Trial conduct will be audited once in a year by the DMC, the process will be independent from investigators and the sponsor.

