### Sample size estimation

Sample size is estimated using G*Power software based on parameters derived from a study with similar design (
Jeffries *et al.*, 2020) effect size d = 0.59, α = 0.05, two-tailed, power (1 − β) = 0.95. The calculation yielded a requirement of n = 100 analyzable participants (50 per group). To account for an anticipated post-randomization attrition rate of 30%, the recruitment target was inflated using the standard formula N_randomized = N_completers ÷ (1 − attrition rate), giving 100 ÷ 0.70 ≈ 143 participants to be randomized. A final sample of 144 participants will therefore be recruited, with 72 participants in each arm.

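### Interim results may change the design or sample size with no limit to blinded data and no error-controlling method, so the planned two-sided 0.05 level is not assured

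*Protocol article*

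**What the plan says.** Three places in the protocol article bear on this.

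- **Data analysis, purpose of the interim.** The DMC has access to interim results and may end the trial for unacceptable morbidity or mortality. A separate sentence gives a second use: "Information obtained from the interim analysis may be used for enhancing trial efficiency by updating design and/or sample size adjustments".
- **Data analysis, who decides.** Of such changes it says: "this will be done as per the suggestions of DMC and after due approval from the funding agency". The decision therefore rests on a committee suggestion and funder approval. No trigger, timing, cap or type of interim information is given.
- **Sample size estimation.** The trial is planned as a single fixed-sample comparison with "effect size d = 0.59, α = 0.05, two-tailed, power (1 − β) = 0.95", leading to 100 analysable and 144 randomised participants.

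The final analysis is described as intent-to-treat with a mixed model. No significance level for it is stated, either kept at 0.05 or adjusted.

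**The concern.** A fixed-sample test at 0.05 has a 5% error rate only if the sample size does not depend on the observed treatment effect. Suppose someone sees the between-arm result, enlarges the trial when the result is weak, leaves it alone when the result is strong, and then applies the usual critical value. The chance of a false positive then exceeds 5%.

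The sentence quoted above permits exactly that, and its aim is efficiency rather than safety. It equally permits harmless changes, such as re-estimating from a pooled SD. The fault lies in a permission that is written down and does not separate the two. At stake is whether a positive result on cigarettes per day could be read at the level for which the trial was planned.

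**Working it through.** **The plan's own figure.** The protocol gives no error rate under adaptation. Its only related figure is the sample size. With d = 0.59, two-sided 0.05 and power 0.95, the normal formula gives n per group = 2 × ((1.960 + 1.645)/0.59)² = 74.7, so 75 (76 by the t-test). The plan states 50. That is a separate discrepancy, and nothing below depends on it.

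**Inputs.** From the protocol: two-sided 0.05 (critical value 1.960), planned power 0.95 and 72 randomised per arm. Assumed, because the protocol is silent: one interim at half the planned information, a change driven by the between-arm effect, and an unadjusted final test.

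**Conditional error.** Let z₁ be the interim statistic, t = 0.5 the information fraction, and R the final size as a multiple of plan. Under the null, the chance of rejecting at the end given z₁ is

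Φ(−(1.960√R − √t·z₁)/√(R − t)) + Φ((−1.960√R − √t·z₁)/√(R − t)).

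Examples:

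- z₁ = 0.5: with R = 1 the terms are Φ(−2.272) + Φ(−3.272) = 0.012. With R = 2 they are Φ(−1.974) + Φ(−2.552) = 0.030. Doubling raises the error.
- z₁ = 2.5: 0.393 with R = 1 and 0.206 with R = 2. Doubling lowers it.

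Choosing R after seeing z₁ can therefore push the error up. Averaging over z₁ ~ N(0,1) gives the overall rate.

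**Ordinary re-estimation, increase only.** With n₁ = 36 per arm at the interim, the observed effect is d̂ = |z₁|/√(36/2). The new size per arm is 2 × ((1.960 + 1.645)/d̂)², held between 72 and the cap.

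| Cap (× plan) | Two-sided type I error |
|---|---|
| 1.5 | 5.3% |
| 2 | 5.5% |
| 3 | 5.9% |

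Using 50 per arm as the plan instead of 72 gives the same figures to this precision.

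**Worst-case choice.** Here R is chosen at each z₁ to maximise the conditional error.

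| Allowed final size (× plan) | Two-sided type I error |
|---|---|
| 1 to 1.5 | 5.8% |
| 1 to 2 | 6.2% |
| 1 to 3 | 6.6% |
| 0.75 to 2 | 7.0% |
| any size from the interim on | about 11% |

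As a check on the last row, the closed form for one tail is 0.025 + exp(−1.960²/2)/4 = 0.0616. Twice that, 12.3%, is a ceiling, because one choice of R cannot be the worst for both tails at once.

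**Rules that do no harm.**

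- Doubling the size only when conditional power is 50% to 95% gave 4.4% in simulation, even with the naive final test.
- A combination test with fixed weights gave 5.0%. The second-stage statistic is standard normal under the null whatever the second-stage size.
- Re-estimation from pooled data would be expected to stay near 5%; this was not simulated.

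**The case against.** **The final level is not stated.** A reader might infer that the final test will stay at 0.05 without adjustment. The documents do not say so: 0.05 appears only as an input to the sample size calculation, and an analysis plan or DMC charter that is not shown could set a combination test. This stands, and it is why the conclusion is that the level is not assured, not that it is breached.

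**The interim may not compare arms.** The only stopping ground named is safety, and re-estimation from pooled SD or attrition fits the wording. This stands too. A reader might also infer an interim efficacy test with its own inflation, but the text describes none, so no figure for one is given. The statement under Study setting that data analysts stay blind does not settle the matter, because an analysis with masked arm labels still shows the size of the difference.

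**Detail belongs elsewhere.** An article may leave the method to a fuller document. That answers a complaint about missing detail. It does not answer one about a permission that is present, that has efficiency as its stated aim, and that neither requires nor refers to a controlling method.

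**Changes would be visible.** Under the Ethics statement, major amendments go to the ethics committee and registries. That makes a change open, but it does not control the error rate.

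**The funder's role.** A reader might infer that routing changes through the funding agency leaks the interim effect and compromises the trial. The text sends the funder a request, not results, and a funder would have to approve a larger trial under blinded re-estimation as well. Leakage is possible if a request follows the observed effect, but it is not shown.

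**Conclusion.** The point holds in a limited form. The protocol permits open-ended design or sample size changes from interim results, and nothing it states preserves the two-sided 0.05 level used for planning.

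The inflation needs two things that the document neither states nor excludes: a change driven by the between-arm effect, and an unadjusted final test. With both, and an interim at half the information, the realistic size is modest, at about 5.3% to 5.9%. The worst choice within one to two times plan gives 6.2%. The figure of about 11% needs someone who picks any second-stage size for each interim result, so it is a bound and not a forecast. These figures cover sample size only; the permission also names the design, and the effect of design changes is not bounded here.

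This should be corrected, but given the conditions and the realistic size it does not rank among faults that would by themselves invalidate the trial.

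**What to change.** Replace the sentence under Data analysis with wording such as: *The interim analysis is for safety. Sample size may be re-estimated once, from the pooled (blinded) SD of cigarettes per day and the pooled attrition rate only. No between-arm efficacy result will be used to change the design or sample size, and none will be shown to the investigators or the funding agency.*

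If unblinded re-estimation is wanted, fix in advance an inverse-normal combination test, Z = √w₁·Z₁ + √w₂·Z₂ with w₁ + w₂ = 1. The weights come from the originally planned stage sizes and stay unchanged whatever the final size. State the timing and the cap as well.

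The cost is protocol wording, settled before any interim look. Under the blinded option the sponsor gives up the freedom to adapt to the observed effect.

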### Intervention

The yoga sessions would be supervised by a certified yoga therapist. Details regarding Y-BLISS intervention is provided in
Table 2.

**Table 2. T2:** 12-minute Y-BLISS Program details.

SL.NO.	Practice	Number of cycles	Duration (minutes)
1	Shighra Vishranti Kriya - Instant Relaxation Technique (IRT)	1	1
2	Shvasa Kriya - Deep Belly Breathing (Inhale:Exhale) (6:4:8:4)	5	2
3	Kapalabhati -Forehead Shining Breath	1 cycle 40 strokes	1
4	Bahya Kumbhaka in Dhyana Mudra–External retention of breath	1	1
5	A-U-M Chanting in a single breath (ratio 1:1:1)	5	2
6	Nadi Shuddhi/Alternate nostril breathing (with mental mantra chant)	6	3
7	Breath awareness in Dhyaan mudra – “Breath in - I am not the body; Breath out – I am not the mind” Positive affirmation in deep silence - “I am happy, healthy and satisfied.”		2

The participants will be taught a 12-minute Y-BLISS program every day in the morning before breakfast for 5 days a week for 8 weeks via an online video-conferencing platform. Initial one week (5 sessions) will be required to train the participants in the program after that a video along with a YouTube link (
https://youtu.be/L6mN9GOXrbY) of the program will be shared with the participants and they will be asked to practice the program as and when required whenever they feel excessive craving.

### Control group

Participants will be taught Desktop exercise (D-exercise) program every morning. The delivery of the D-exercise program will match that of Y-BLISS program in all the aspects related to the mode of delivery, duration, therapist interaction, content, flow and follow-up of the program.
Table 3 provides the required details.

**Table 3. T3:** 12-minute desktop exercise (D-exercise) module.

Desktop exercises module			
Sl No		No of cycles	Duration
	**Stretches**		
1	Neck Rolls	5 Round	30 sec
2	Shoulder Rolls	5 Round	30 sec
3	Chest Stretch	5 Round	30 sec
4	Upper Back Stretch	5 Round	30 sec
5	Hamstring Stretch	5 Round	30 sec
6	Bent-Knee Stretch	5 Round	30 sec
	**Core**		
1	Seated Bicycle Crunches	5 Round	1 min
2	Lower-Abs Leg Lifts/one and two legs	5 Round	1 min
3	Oblique Twists	5 Round	1 min
	**Upper Body**		
1	Arm Circles	5 Round	30 sec
2	Desk Push-Ups/Wall Push-Ups	5 Round	30 sec
3	Arm Pulses		
	**Lower Body**		
1	Calf Raises	5 Round	30 sec
2	Wall Sits	5 Round	30 sec
3	Lunge	5 Round	30 sec
4	Chair Squats	5 Round	30 sec
	**Cooling down**		
1	Sit relaxed with closed eyes and consciously try to relax body muscles from head to toe		3 min

### Adherence monitoring

Adherence will be monitored identically in the Y-BLISS and D-exercise arms. Attendance at each of the 40 scheduled supervised online sessions will be recorded by the instructor delivering the session. As-needed self-practice outside the supervised sessions will be captured through weekly SMS-based self-report of the number of sessions practised, collected alongside the number of cigarettes smoked per day.

Three adherence metrics will be reported for each arm: mean supervised sessions attended out of 40, mean self-reported self-practice sessions, and total exposure as the sum of the two. A completer will be defined a priori as a participant attending at least 50 percent of supervised sessions, that is 20 of 40, and completing the week 8 assessment. Because self-practice is self-reported and cannot be independently verified, it will be reported descriptively as a secondary adherence indicator, and this is acknowledged under Limitations.

## Description of some major assessments

### Motivation To Stop Smoking (MTSS) scale

The scale consists of 7 item questionnaires, effectively combines both current desire and intention to stop smoking – two key components of motivation into one single response scale, ranging from 1 (lowest) to 7 (highest level of motivation to stop smoking) (
Smit *et al.*, 2011).

### Heaviness of Smoking Index (HSI)/Smoking rate

The scale consists of a 2-item questionnaire. It measures the Heaviness of Smoking Index (HSI), time to first cigarette of the day (TTFC) and daily consumption (cigarettes per day [CPD]). These are strong predictors of quitting behavior (
Borland *et al.*, 2010).

### Fagerstrom Test for Nicotine Dependence [FTND]

The Fagerström Test for Nicotine Dependence contains six items to evaluate quantity of cigarette consumption, dependence and compsulsion to use. It is a standardized tool used extensively in research related ti nicotine dependence. Higher score on the scale indicates higher dependence on nicotine (
Heatherton *et al.*, 1991).

### Peak flow meter

This device measures the force of exhaled air in liters per minute. It is an indicator of lung functions. This device is portable, easy to use and scientifically validated (
Dekker *et al.*, 1992).

### Exhaled carbon monoxide

CO biomarker is well-established with recent tobacco use and to distinguish tobacco users from nonusers, responding to cessation and reduced use, and having a dose-response with tobacco use. CO analyzer machines calculate CO in ppm in expired air. Some CO analyzer machines automatically calculate the Carboxyhemoglobin percentage based on the levels of CO in the expired air. Interpretation CO levels in parts per million is 1–6 is minimal exposure, 7–10 is Second hand, exposure-11 or more is Regular smoker (
Saloojee & Russell, 1980).

### Seven-day point-prevalence abstinence (7PPA)

The 7-day point-prevalence abstinence (7PPA) will be defined as self-reported complete abstinence during the 7 days preceding assessment, biochemically verified using exhaled carbon monoxide levels (≤10 ppm indicating abstinence). 7PPA will be assessed at baseline, week 4 and week 8, in parallel with the other outcome measures.

The 10 ppm threshold is adopted in preference to a stricter cut-off because ambient carbon monoxide in a large metropolitan setting can raise expired air values independently of active smoking, so that a lower threshold risks misclassifying abstinent participants as smokers. Abstinence will additionally be examined at a 6 ppm threshold as a sensitivity analysis.

## Ethics statement

The proposed study has been approved by the Institutional Ethics Committee (RES/IEC-SVYASA/255/2022 dated 17
^th^ August 2022) and registered with CTRI (REF/2022/10/059103), date of registration: 14
^th^ December 2022. Written Informed consent will be taken from all participants by the investigator, and study records will be kept confidential. Subject identifying information will be replaced with codes. Major amendments to the protocol (changes to eligibility criteria, outcomes, analyses) will be communicated to investigators, institutional ethics committee, and trial registries. The study protocol has been prepared using SPIRIT checklist and the trial has been registered under the centre for open science with registration number:
https://osf.io/p2a4w.

## Compensation for loss of time/wages

No Compensation provided.

### Limitations

The assessment schedule of this trial spans baseline, week 4 and week 8, and the design does not extend beyond the end of the 8-week intervention. Because relapse risk is concentrated in the months following a quit attempt, and because the convention in cessation research is biochemically verified abstinence at six months or longer, the trial is positioned to support conclusions about end of treatment reduction in the number of cigarettes smoked per day and short-term point-prevalence abstinence rather than about sustained cessation. Assessment at 3, 6 and 12 months lies outside the scope and resourcing of the present efficacy trial and is planned as a separate follow-on study.

Eligibility excludes severe and unstable psychiatric illness on grounds of safety and feasibility, since the intervention includes unsupervised as-needed practice that requires reliable self-monitoring, and since active severe illness would confound both adherence and the craving and dependence outcomes. This limits generalizability, because depressive, anxiety and psychotic disorders are considerably more prevalent among people with tobacco use disorder than in the general population. Participants with stable, treated depressive or anxiety disorders on unchanged pharmacotherapy remain eligible, so the sample retains part of that comorbidity, but the findings should not be extended to people with active psychosis, bipolar disorder or a current severe depressive episode, for whom a supervised adaptation of the intervention would be required.

Two further boundaries of the design are noted. Cumulative nicotine replacement therapy exposure is not quantified prospectively and within-trial dose changes are not modelled as time-varying covariates, so residual confounding arising from variation in pharmacotherapy cannot be excluded; future trials of this kind should capture cumulative exposure prospectively. Self-practice outside supervised sessions is captured by self-report and cannot be independently verified, and is therefore treated as a secondary adherence indicator rather than as a primary measure of exposure.

### Implications

This prospective randomized trial will attempt to replicate and confirm the utility of Yoga in the clinical management of TUD, which has worldwide relevance. The study may also help establish a neurobiological basis for the effects of Yoga in substance use disorders.

### Plans for data management, sharing and dissemination of research findings

All information pertaining to the participants would be kept confidential under the researchers. For conducting the study, each participant would be number coded instead of their name which would be only available to the researchers. Barring the Principal investigator and the study coordinator, none will have access to the final trial dataset.

## Dissemination policy

The findings obtained from the study will be shared with participants. As mentioned above no confidential information will be shared. Data will be published in a peer-reviewed scientific journal along with presentations at conferences for spreading and discussing the findings of the study.

## Data availability

### Underlying data

No data are associated with this article.

### Reporting guidelines

OSF: SPIRIT checklist and flow chart for ‘Efficacy of yoga-breath linked intervention to stop smoking (Y-BLISS) in reducing number of cigarettes smoked per day among smokers attempting to reduce or quit: Study protocol for a randomized controlled trial’.
https://doi.org/10.17605/OSF.IO/P2A4W (
[name] *et al.*, 2024).

Data are available under the terms of the
Creative Commons Attribution 4.0 International license (CC-BY 4.0).
